#### Randomization

After baseline assessment has been completed by the adolescent, randomization will be carried out. Randomization of participants will be performed via Castor EDC (Castor Electronic Data Capture (2021.2)) by a researcher who is blind to block size and order. Randomization will take place at an individual level, stratified by primary diagnosis (depressive or anxiety disorder) and treatment site using a computer-generated block randomization schedule. To ensure that an equal number of patients are allocated to CBT and CBT + E-TRAIN, the allocation ratio will be 1:1. To prevent selection bias, all researchers will be blind to random block order. No researchers will have access to the randomization schedule. Due to the nature of the add-on design, blinding of adolescents, parents, therapists, and researchers to treatment condition is not applicable. The research assistants assessing the diagnostic interview at T2 will be blinded to treatment condition.

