Since ER seems to be an important transdiagnostic factor across depressive and anxiety disorder [26], enhancing ER might be a promising target in the treatment of these disorders. In an RCT among depressed adults, adding an emotion regulation training to CBT resulted in a significant decrease in depressive symptoms compared to CBT alone [40]. Little research has been conducted on ER interventions in adolescent samples with anxiety and depressive disorders. Holmqvist Larsson et al. [41] showed that a group skills training in ER for adolescents and their parents led to a decrease in ER difficulties in an outpatient sample of adolescents with a mental disorder. Furthermore, in a recent review on emotion regulation focused interventions four studies that include adolescents with internalizing disorders are discussed [34]. In all four studies, adding an ER regulation component to the intervention led to improvement of ER skills in adolescents [42–45].

We developed a guided internet-based emotion regulation training called *E-TRAIN* that will be added to Cognitive Behavioral Therapy (CBT). Internet-based treatments may provide an accessible and feasible alternative to face-to-face treatments: they fit to the digital lifestyle of adolescents, are less time-consuming, and show advantages in terms of convenience [46, 47]. Moreover, numerous meta-analyses have demonstrated that internet-based therapy is effective in treating depressive and anxiety disorders in children and adolescents [48–51]. We decided to create a guided intervention because there is meta-analytical support of the superiority of guided internet-based treatments to unguided treatments in terms of efficacy and acceptability in adults [46, 52, 53]. For adolescents with anxiety and/or depression, a recent meta-analysis showed that guided internet-based treatments (of at least 90 min) were superior to unguided treatments [50].

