#### Assessments

After signing informed consent, all participants will be invited to fill in the baseline assessment (T0). Adolescents and their parents will receive an email with a link to the questionnaires. All assessments will be conducted via the internet, using Castor EDC (Castor Electronic Data Capture (2021.2)). Those who have not completed the assessment within five days will receive a reminder via email. After one week, participants who have not completed the assessment will be approached via telephone by a research assistant. If necessary, adolescents will have the opportunity to fill in the baseline assessment in the presence of a research assistant, who can provide guidance. After completing baseline assessment, participants will receive a voucher of 15 euros.

Follow-up assessments will be administered at 3 months, 6 months, and 12 months after baseline. Similar to the procedure for baseline assessments, participants (adolescents and parents/caregivers) who have not completed the assessment after one week will be reminded via email and telephone. After completing follow-up assessments, participants (adolescents and parents) will receive a voucher of 10 euros for each completed T1 assessment, and 15 euros for each completed T2 and T3 assessment. Additionally, after completion of the T2 assessment, a trained research assistant who is blind for treatment condition will contact each adolescent for a short diagnostic interview by phone to determine the presence of depressive and anxiety disorders at 6-month follow-up. The depression and anxiety sections of the MINI (KID) will be used. After completion of the MINI (KID), each participant will receive a voucher of 5 euros. Both the E-TRAIN and the CBT therapist of the adolescent will fill in short questionnaires as well. The CBT therapist will be asked to complete questionnaires at T0, T1, and T2, and the E-TRAIN therapist will fill in a questionnaire after completion of E-TRAIN.

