### Data analyses

#### Primary outcome measures

Linear mixed models will be used to determine the effectiveness of adding E-TRAIN to CBT in reducing depressive and anxiety symptoms (measured with the RCADS25). A two-level structure will be used (Level 1: repeated measures, Level 2: patients). The overall treatment effect will first be evaluated in a model with condition and the baseline value of the outcome. Second, between-group differences at each time-point will be examined by adding time and the interaction of time and condition to the model. Time will be treated as a categorical variable, represented by dummy variables. Furthermore, as a sensitivity analysis, we will fit a model adjusted for the total number of completed CBT sessions and other potentially relevant confounders. Imputation of missing data will not be necessary because we will use mixed-model analyses, which adequately handles missing values [98]. Analyses will be conducted on the entire randomized sample (i.e. intention to treat) and on the per protocol/treatment completers sample. For the treatment completers sample of the experimental (E-TRAIN) condition, adolescents who completed ≥ 66% of the online sessions (four sessions or more) will be regarded as completers. The aforementioned main analyses will also be conducted separately for those with a primary diagnosis of depressive disorder, and for those with a primary diagnosis of anxiety disorder. Analyses will be conducted using SPSS version 26 + and R version 3.0 + . Statistical significance will be set at α < 0.05.

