## Data Availability

During the ongoing data collection researchers will only have restricted access to the data. After completion of the study, only the Principal Investigator [name] and the Study Coordinators (JE and MW) will have access to the data. Raw data cannot be made openly accessible to the public, due to privacy concerns. After request to the corresponding author, the data, statistical parameters and statistical code will be made accessible. Results will be published in international peer-reviewed journals and will be presented at scientific conferences. We will also report our results to relevant stakeholders in newsletters and trial summaries. All participants and parents will receive a written summary of the results after completion of the study. The publication of the results will be independent of the results, whether or not the experimental intervention is effective. Eligibility of authorship will be decided according to the guidelines of the International Committee of Medical Journal Editors (ICMJE). In accordance with the national regulations in The Netherlands, data will be stored for 15 years.

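### The add-on design is given as the reason for blinding no researchers, but that reason does not reach staff who analyse coded data or make the T1–T3 reminder calls

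*Protocol article*

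**What the plan says.** All references are to the protocol article; no separate analysis plan was available.

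- **Randomization.** "Due to the nature of the add-on design, blinding of adolescents, parents, therapists, and researchers to treatment condition is not applicable". One exception follows: "The research assistants assessing the diagnostic interview at T2 will be blinded to treatment condition". The section also protects the allocation sequence: "No researchers will have access to the randomization schedule".
- **Assessments.** At baseline, "After one week, participants who have not completed the assessment will be approached via telephone by a research assistant". For T1 to T3 the procedure is described as similar, and adolescents and parents "who have not completed the assessment after one week will be reminded via email and telephone". Blinding is mentioned only for the T2 diagnostic interview.
- **Data analyses, Primary outcome measures.** The main mixed model contains condition and the baseline value; time and its interaction with condition are then added. As a sensitivity analysis the team will fit "a model adjusted for the total number of completed CBT sessions and other potentially relevant confounders". Intention-to-treat and completer samples are both analysed.
- **Data Availability.** During collection, "researchers will only have restricted access to the data". Afterwards, access is limited to the principal investigator and the study coordinators. Masked arm codes are not mentioned.
- **Background.** The authors state: "We developed a guided internet-based emotion regulation training called" E-TRAIN.

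**The concern.** A waiver of blinding should be argued role by role. Adding E-TRAIN to CBT plainly reveals the arm to the adolescent, the family, the therapists and whoever schedules the training. It reveals nothing to a person fitting a model to a dataset with a two-level arm code, or to a person working through a list of overdue questionnaires. The protocol uses one reason for all of these people.

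Two things are at stake. First, an analyst who sees which arm is which can lean, even unintentionally, toward the specification that favours E-TRAIN. Second, a caller who knows the arm can chase one arm harder, which could make follow-up unequal. The sample size section allows 35% extra inclusion for drop-out, so incomplete follow-up is expected. The primary outcome is self-reported by adolescents who know their treatment. That makes the safeguards which remain possible worth keeping.

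**Working it through.** **Step 1. Does the stated reason cover each role?** The plan gives no figure for this point, so the first check sets the text side by side.

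| Role | Does the add-on design reveal the arm? | What the article states |
|---|---|---|
| Adolescents, parents, therapists | Yes | Not blinded |
| Staff who allocate participants or arrange E-TRAIN | Yes | Covered by the blanket term for researchers |
| T2 interviewers, who speak to adolescents by phone | Not inherently | Blinded |
| T1–T3 reminder callers | Not inherently | No blinding stated |
| Analysts of coded data | No | No masking stated |

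The third row decides the matter. If staff who hold a diagnostic conversation with the adolescent can be blinded in this design, the design is no obstacle to masking a coded export or a call list. Hiding the schedule and block order is a different protection: it conceals the next allocation, not the arm already assigned.

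**Step 2. How much freedom is left?**

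- Fixed: the RCADS25 total score, T2 as primary time point, the mixed model with baseline value, categorical time, no imputation, and four or more sessions for completers.
- Open: the unnamed confounders of the sensitivity model, and the weight given to the overall effect versus the T2 effect and to intention to treat versus completers.

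**Step 3. Illustration of size.** These inputs are assumptions, not figures from the protocol: four candidate covariate sets for the same T2 contrast, no true effect, and test statistics *z*₁ to *z*₄ with common correlation *r* of 0.98, 0.95 or 0.90. Positive *z* favours E-TRAIN and the threshold is 1.96.

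Probability that the set most favourable to E-TRAIN gives a false claim of benefit:

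P(max *z* > 1.96) = 1 − ∫ Φ((1.96 − √*r*·*u*)/√(1 − *r*))⁴ φ(*u*) d*u*

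Probability that the most significant set, in either direction, is significant:

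P(max |*z*| > 1.96) = 1 − ∫ [Φ((1.96 − √*r*·*u*)/√(1 − *r*)) − Φ((−1.96 − √*r*·*u*)/√(1 − *r*))]⁴ φ(*u*) d*u*

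| *r* | False benefit, best of four | Most significant of four, either direction |
|---|---|---|
| Single fixed model | 2.5% | 5.0% |
| 0.98 | 3.4% | 6.8% |
| 0.95 | 4.0% | 8.0% |
| 0.90 | 4.7% | 9.4% |

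**Step 4. What each safeguard removes.** The right-hand column does not depend on arm labels: an analyst who sees only X and Y can still pick the largest |*z*|. By symmetry half of those errors favour each arm, for example 6.8%/2 = 3.4%. Masking therefore removes the ability to steer toward E-TRAIN, but does not by itself restore 2.5%. Settling the covariates before any model is run does that.

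**The case against.** The case against is substantial.

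- **The main analysis is specified.** The open covariates belong to a model labelled as a sensitivity analysis. Reporting the best of several covariate sets as the primary result would depart from the written plan. This stands, and it bounds the concern.
- **The analyst is not named.** The sentence sits in the Randomization section and may have been written with allocation staff in mind. A reader might infer that E-TRAIN's developers will choose analysis options with the arms in view. The shared authorship and the limits on data access make that possible, but the article does not say it.
- **Callers are not said to see allocation.** The one-week trigger is the same for everyone, and baseline calls precede randomization. Research assistants may also be meant as a group separate from researchers. This stands as a limit: only T1 to T3 are affected, and only as a possibility.
- **Other protections exist.** The T2 interview is blinded, data and code are to be available on request, and publication is promised whatever the result.
- **An unseen analysis plan may provide for masking.** It may. The point here is not an omission, however. The article states positively that blinding of researchers is not applicable, for a reason that does not fit all of them. A plan that masked the analyst would need that sentence changed.

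**Conclusion.** The sentence in the Randomization section is too broad. The add-on design does not justify leaving analysts of coded data or T1–T3 reminder callers unblinded, and the blinded T2 interviewers show as much. The consequence is that these staff could know the arm, not that they will know it or act on it.

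The size is moderate at most. Under the assumptions of four covariate sets and correlations of 0.98 to 0.90, false claims of benefit rise from 2.5% to between 3.4% and 4.7%. That applies only if an adjusted model chosen after seeing results is given weight as evidence. The 6.8% to 9.4% should not be read as the type I error of the primary analysis, nor as what masking would prevent: the main model is fixed, and those figures are unaffected by relabelling the arms. No size can be put on the reminder-call route from the article. Neither safeguard touches bias from self-report by adolescents who know their treatment.

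**What to change.** Remove researchers from the list of people for whom blinding is declared not applicable, keep the sentence on the T2 interviewers, and add text along these lines:

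> Staff who deliver or arrange E-TRAIN are not blinded. The covariates and missing-data handling of the T2 RCADS25 models are fixed before any model is run. These models are run on an export with recoded participant identifiers, arms coded X and Y, and no fields that exist only for E-TRAIN (platform log data, CSQ-8, SUS). The arm code is broken afterwards. Reminder call lists do not show allocation.

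The order matters: covariates first, then the masked run, then unmasking.

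The cost is wording, a recoded export from the existing data system, and call lists without the allocation field. Treatment, assessments and participant numbers do not change. There are two small downsides. Completer and uptake analyses wait until the code is broken. Analysts who already know individual allocations are masked only if participant identifiers are recoded as well; if the few people with access could still recognise participants, someone else may have to run these models. The article reports recruitment as ongoing, so the change could still apply to remaining follow-up and to the analysis.

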#### Focus groups

Additionally, we will organize two focus groups to evaluate the experimental intervention. We aim to include six randomly selected participants for each focus group. Adolescents who participate in the focus group will receive a voucher of 25 euros. Focus groups will take approximately 1.5 h, and will be led by a psychologist and a researcher. In addition, we will organize a focus group with a random sample of six E-TRAIN therapists to examine the acceptability of the internet-based emotion regulation training.

### Interventions

#### E-TRAIN

Adolescents allocated to the experimental condition will partake in a guided internet-based emotion regulation training (E-TRAIN), that was developed for the purpose of the current study. E-TRAIN is based on existing face-to-face emotion regulation interventions for children and adolescents [57, 58], adults [33], and a recently developed internet-based emotion regulation training for depressed adults [59]. In order to develop an internet-based module tailored for adolescents, we first performed a pilot feasibility study using a brief, existing internet-based emotion regulation training module [60] among our target population at the youth mental health care department of Arkin. We conducted focus groups with pilot participants (*N* = 5) and youth therapists (*N* = 6) aimed at 1) evaluating the brief emotion regulation module; 2) identifying key strategies for improvement; and 3) identifying adolescents’ preferences and needs regarding internet-based treatment. Based on the existing emotion regulation interventions and the conclusions provided by these focus groups, we developed a first version of the E-TRAIN module. Subsequently, this version was tested and evaluated by a small sample of adolescent patients with anxiety and/or depression (*N* = 4), after which we further adapted and finalized the E-TRAIN module.

E-TRAIN will be provided on a secured online platform (*Jouw Omgeving*). It consists of six sessions in which six ER skills are covered: 1) relaxation; 2) non-judgmental awareness of emotions; 3) acceptance of emotions; 4) self-support; 5) analyzing emotions; and 6) modifying emotions. Adolescents receive psycho-education about these skills, and about the origin and functions of emotions in animated videos (of 1–5 min). Moreover, each session includes short written texts, exercises, relevant examples, patient stories, and audio files. By listening to these audio files, the adolescent can practice with the newly acquired ER skill and previously acquired skills. After each session, the adolescent is stimulated to listen to this audio file at least three more times before the next session as a homework assignment. See Fig. 2 for more detailed information on each session. Each E-TRAIN session will take approximately 25 min to complete. After each session a trained therapist will provide feedback on the exercises, using a secured chat function within the online platform, to guide the adolescent in correctly applying the learned ER skills.

**Fig. 2 Fig2:**
[figure not shown]
Summary of E-TRAIN sessions

Additional to these six online sessions, E-TRAIN consists of three video conference sessions with a therapist. At the start of E-TRAIN, a video conference session of 30 min will be scheduled. This video conference session will be held in order to acquaint patients with their therapist and vice versa, and to determine E-TRAIN treatment goals. After finishing the first three online sessions, a second video conference session will be scheduled to provide guidance and monitor the patient's progress. At the end of E-TRAIN, a final video conference session will be scheduled. In this session, the treatment goals will be evaluated and the focus will be on applying the learned emotion regulation skills in daily life.

#### E-TRAIN therapists

Patients will be guided by a psychologist who has been trained in the application of E-TRAIN. After each online session, these E-TRAIN therapists will provide feedback and guidance using secured messages within the online platform. To ensure treatment integrity, E-TRAIN therapists will receive a detailed treatment protocol with standardized feedback templates. E-TRAIN will take place simultaneously to CBT, and will start after the first 2–4 CBT sessions. Based on the patient’s preference, the six sessions of E-TRAIN will be completed on either a weekly or fortnightly schedule; hence, E-TRAIN will be completed in 6 to 12 weeks. All adolescents will be guided by an E-TRAIN therapist other than their CBT therapist.

#### Treatment as usual: CBT

Both groups will receive CBT, a commonly used evidence-based therapy for adolescents with anxiety [61] and depression [62, 63]. CBT will be provided by experienced MSc or registered Health Care psychologists. The primary goal of CBT is to identify and restructure maladaptive thought patterns and behaviors (e.g., [64, 65]). Key components of CBT for adolescents with depressive and anxiety disorders are 1) psychoeducation; 2) behavioral activation, exposure, and behavioral experiments; 3) cognitive restructuring; and 4) relapse prevention [65, 66].

### Outcome measures

#### Primary outcome measure

Depressive and anxiety symptoms as a unidimensional construct will be measured with the child self-report version of the Revised Children’s Anxiety and Depression Scale – Short Version (RCADS25) [67]. This questionnaire is recommended by the International Consortium for Health Outcomes Measurement (ICHOM) as a questionnaire for measuring anxiety and depression in children and adolescents [68]. The RCADS25 assesses anxiety and depression according to the DSM-IV and consists of two subscales: the 15-item anxiety subscale and the 10-item depression subscale [67]. The total score on the RCADS 25 will be used. The questionnaire has shown a good internal consistency (α = 0.89) (Bagheri et al., 2019), and acceptable reliability and validity [67].

#### Key secondary outcome measures

See Table 1 for an overview of all measurement instruments and timepoints for adolescents, parents/caregivers, and therapists.

**Table 1 Tab1:** Overview of instruments per assessment

**Measures**	**T0**	**T1**	**T2**	**T3**^**a**^
*Patient*				
Demographics	x			
RCADS25	x	x	x	x
CDI-2	x	x	x	x
SCARED	x	x	x	x
FEEL-KJ	x	x	x	x
DERS	x	x	x	x
AUDIT	x	x	x	x
SRSQ	x	x	x	x
IPPA short form	x		x	
RSES	x		x	
Life Events	x			x
COVID-19		x	x	x
CSQ-8			x^b^	
*Parent*				
Demographics	x			
CDI-P	x	x	x	
SCARED-P	x	x	x	
FEEL-KJ-P	x	x	x	
DERS	x	x	x	
CCNES-A	x		x	
BSI-18	x			
*CBT therapist*				
CGI	x	x	x	
CGAS	x	x	x	
*E-TRAIN therapist*				
SUS			x	

^a ^T0: baseline, T1: 3 months after baseline, T2: 6 months after baseline, T3: 12 months after baseline

^b ^Will only be assessed in the E-TRAIN (experimental) group

##### Depressive symptoms

Depressive symptoms as a separate construct will be measured with the Children’s Depression Inventory (CDI-2; Dutch version) [69]. The 28-item CDI-2 is a revision of the CDI [70] that assesses affective, cognitive, and somatic symptoms of depression in youth (7 to 17 years) over the past two weeks [69]. All 28 items are rated on a 3-point Likert scale from 0 to 2, and scores range from 0 to 56. The CDI-2 shows good psychometric properties [71, 72], and has been validated in adolescents up to the age of 21 [69]. To obtain a multi-informant assessment of adolescents’ depressive symptoms, the parent version of the CDI-2 will be used to asses depressive symptoms according to the parent (CDI-P) [70]. The CDI-P comprises of 17 items rated on a 4-point Likert scale, and shows good psychometric qualities [72].

